### Sample Size

Statistical considerations underlying this sample size calculation are based on the null hypothesis that there is no difference in pain intensity between the study treatments and the alternative hypothesis that melatonin is different from placebo. Systematic reviews of placebo-controlled chronic pain trials consistently reveal that significant differences between treatment and placebo groups vary between 0.5 and 1.5 points, depending on the magnitude of the placebo response in any given trial [22]. Thus, based on a previous estimated within-participant variation of 2.5 from studies on NP [26], we project that a sample size of 21 participants would allow for an 80% chance of detecting (α=.05) a mean treatment group difference of 1.5 points on a 0-10 numerical rating scale. In order to have a sample size divisible by 4, we have adjusted the sample size to 24 participants. Accounting for trial dropout rates from our previous trials and for a 2-period crossover design, we expect that the recruitment of 30 enrollees for each trial will yield the aforementioned number of completers.

### Statistical Analysis

Participants who complete both treatment periods will be included in trial analyses. When data from only one period are available, sensitivity analysis including all participants will also be performed, by assuming some reasonable but extreme values for the remaining periods. Those receiving at least one dose of study drug will be included in the safety analyses. The primary outcome will be calculated as an average of pain scores as recorded in the participant pain diaries within the last 7 days (at MTD in week 4 of the treatment), if more than 50% of the information (at least 4 days) is not missing [39]. Otherwise, mean daily pain will be treated as missing data. Sensitivity analyses based on the average of all available pain scores will also be performed to confirm the results of the primary analysis. A linear mixed model with sequence, period, treatment, and the first-order carryover effects as fixed effects and participant as a random effect [39] will be used to test whether there is any treatment difference among groups and to estimate the least squares mean of the mean daily pain intensity for each treatment group, adjusting the carryover and period effects. The comparison between melatonin and placebo will be performed on the basis of the least squares means and SDs from the linear mixed model. Sensitivity analyses will be performed using a pattern-mixture model [40] based on patterns of missing data to check the robustness of results in case data may not be missing at random.

Secondary outcomes will be analyzed similarly except that (1) only 1 measurement will be analyzed in the last week for the singular measures (ie, final week questionnaires), and (2) the scoring algorithms developed for the Brief Pain Inventory, the Beck Depression Inventory-II, the Beck Anxiety Inventory, and the SF-36 will be first used to derive the subscales or domains within these instruments, and the scores on these subscales or domains will be used as response variables in the linear mixed model analysis.

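### The primary efficacy set is limited to participants who complete both periods, although the planned mixed model can use one-period data and the restriction can bias the estimate if dropout is unequal between treatments

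*Protocol article*

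**What the plan says.** All of this is in the protocol article.

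- **Primary set** (Statistical Analysis): "Participants who complete both treatment periods will be included in trial analyses". Safety is different: it covers everyone who took at least one dose.
- **One-period participants** (same section): "When data from only one period are available, sensitivity analysis including all participants will also be performed, by assuming some reasonable but extreme values". These values stand in where a period was not observed.
- **Model** (same section): "A linear mixed model with sequence, period, treatment, and the first-order carryover effects as fixed effects and participant as a random effect".
- **Valid period mean** (same section): the week-4 diary scores are averaged "if more than 50% of the information (at least 4 days) is not missing"; otherwise the period mean counts as missing.
- **Data not missing at random** (same section): "Sensitivity analyses will be performed using a pattern-mixture model [40] based on patterns of missing data".
- **Expected loss** (Sample Size): 24 completers are wanted, and "the recruitment of 30 enrollees for each trial will yield the aforementioned number of completers". No dropout rate is stated.
- **Dropout and treatment** (Discussion): early dropout is listed as a threat, and handling of treatment-emergent adverse effects is among the measures expected to limit it.

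**The concern.** Completing both periods happens after randomisation and can depend on what was taken first. A participant who does badly or feels sedated in period 1 may leave before period 2. Removing that participant also removes an observed, valid period-1 result. If this happens more often after one treatment, the remaining participants in the two sequences no longer form a fair comparison.

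The restriction is also unnecessary. A linear mixed model with a random participant effect accepts a participant who has one valid week-4 mean. Under missing at random, it uses that observed result to correct for who left. What is at stake is the headline treatment difference. Planned power is not affected, because the sample size already allows for the loss.

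**Working it through.** **1. The plan's own figures.** Inputs from Sample Size: difference 1.5, variation 2.5, α = 0.05, power 80%. Reading 2.5 as the SD of the within-participant difference (the protocol does not define it):

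n = [(1.960 + 0.842) × 2.5 / 1.5]² = 21.8, so 22, against 21 stated.

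This is close enough to adopt that reading. With 24 completers, t-based power is 80.2%. Implied loss: 1 − 24/30 = 20%, and 24/0.80 = 30 matches the stated recruitment.

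**2. Set-up for the bias.** Assumptions, none given in the protocol:
- 15 participants per sequence, and 6 of 30 leave after period 1.
- Those who leave are the ones with the worst period-1 pain in their sequence.
- True treatment effect 0, no carryover term.
- Between-participant SD (σ_b) from 1 to 2.5.

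The within-participant variance follows from step 1: σ_w² = 2.5²/2 = 3.125. The total variance is σ² = σ_b² + 3.125.

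**3. Formula.** Let d be period-1 pain minus period-2 pain. The completer estimate is half of (mean d in melatonin-first minus mean d in placebo-first). Removing the worst fraction p on period-1 pain lowers the period-1 mean of those left by λ(p)σ, where λ(p) = φ(z₁₋ₚ)/(1 − p). Their period-2 mean falls only by the share σ_b²/σ² of that. So d shifts by −λ(p)σ_w²/σ, and

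bias = −½ × [λ(p_M) − λ(p_P)] × σ_w²/σ,

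with p_M and p_P the fractions leaving after melatonin and after placebo.

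**4. Results.** σ = √4.125 = 2.031 for σ_b = 1, and √9.375 = 3.062 for σ_b = 2.5.

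| Leavers after melatonin : placebo | λ(p_M) − λ(p_P) | Bias, σ_b = 1 | Bias, σ_b = 2.5 |
|---|---|---|---|
| 6 : 0 | 0.644 − 0 = 0.644 | −½ × 0.644 × 3.125/2.031 = −0.50 | −½ × 0.644 × 3.125/3.062 = −0.33 |
| 4 : 2 | 0.448 − 0.248 = 0.200 | −0.15 | −0.10 |
| 3 : 3 | 0.350 − 0.350 = 0 | 0 | 0 |

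A negative value favours melatonin. The formula is a large-sample one. Simulated trials of 30 agree: about −0.48 to −0.32 for 6:0, about −0.16 to −0.10 for 4:2, and about 0 for 3:3. In the 6:0 case the completer analysis has a two-sided type I error of about 9% to 14% instead of 5%.

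**5. Same data, all participants in the mixed model.** The bias is about 0 in every row, because dropout here depends only on a period-1 score that stays in the analysis. In a large simulated sample with σ_b = 1.5 and all dropout after melatonin, completers give −0.43 and the mixed model 0.01 when the truth is 0. When the truth is −1.5, they give −1.95 and −1.51.

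**6. Precision.** With 24 completers the standard error is 2.5/√24 = 0.510. If all 6 leavers each add one valid period, it falls to between 0.488 and 0.502. The gain is therefore almost entirely in bias.

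**The case against.** **The plan already has sensitivity analyses.** It includes an all-participant analysis with extreme values and a pattern-mixture model. A reader might infer that these cannot reveal bias. That goes too far: an extreme-value analysis is a bounding exercise and would give some indication. What stands is that neither changes the set behind the primary estimate.

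**Two stronger readings are not in the text.** A reader might infer that the pattern-mixture model is confined to completers and so has little to model. The article says only that it is a "pattern-mixture model [40] based on patterns of missing data" and names no population. A reader might also infer that the extreme values will be picked after the data are seen. The words "by assuming some reasonable but extreme values for the remaining periods" fix no values, but an analysis plan that is not shown may do so.

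**A 25% overstatement is not supported.** One could argue that if completers gain 1.5 points and the 6 leavers gain nothing, the average over all 30 is (24 × 1.5)/30 = 1.2, so that 1.5 is 25% too high. The arithmetic is right, but it assumes the leavers' effect, and the proposed model does not recover 1.2. With leavers split evenly it gives about 1.38 to 1.45. That figure should not be used to size this point.

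**The bias depends on the mechanism.** This stands. With equal dropout it is nil, and if leavers come mainly from placebo it runs against melatonin. The protocol's dose-reduction provision and weekly contact may keep dropout low. The 20% is a planning allowance, not an observed rate.

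**Context.** The Discussion describes a proof-of-concept trial in which participants serve as their own controls. That lowers the stakes, but the completer rule still gives no protection when dropout is unequal.

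**Conclusion.** The point holds in a limited form. The primary efficacy set is defined by a post-randomisation event, and data that the planned model can use are left to a sensitivity analysis. Under the assumed mechanisms with no true effect, the completer estimate is off by about 0.3 to 0.5 points in melatonin's favour at the one-sided extreme, about 0.1 to 0.2 points for a 4:2 split, and nothing for an even split. For scale, the Sample Size section cites treatment differences from 0.5 to 1.5 points.

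These figures show possible size and do not predict what will happen. They rest on reading 2.5 as the SD of the difference, an assumed between-participant SD of 1 to 2.5, dropout driven by observed period-1 pain, and no carryover term. Sequence and first-order carryover cannot both be estimated in a two-sequence, two-period design; that is a separate matter. The mixed model removes the bias only under missing at random. The change should be made before unblinding.

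**What to change.** - **Primary set:** all randomised participants with at least one valid week-4 mean (4 or more diary days), analysed in their randomised sequence with the same mixed model.
- **Sensitivity:** move the analysis of participants who complete both periods here.
- **Extreme-value analysis:** keep it for all participants, but carry it out as a tipping-point analysis, with a range of shifts in the missing scores set in advance separately for melatonin and placebo. Report where the conclusion changes.
- **Pattern-mixture model:** keep it and state the population to which it is fitted.

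The cost is revised wording and a little programming, with no new data and no extra participants. The estimate may be less favourable to melatonin, and the gain in precision is small. Participants who leave before a valid period-1 week-4 mean add nothing to the new primary analysis without imputation, so fewer than 6 may be recovered. The tipping-point analysis is where they are covered.

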Melatonin (N-acetyl-5-methoxytryptamine), a hormone secreted by the pineal gland, has been implicated in several homeostatic functions including sleep, modulation of circadian rhythms and mood, enhanced immunity, and antioxidant free radical scavenging [13]. Relevant to pain, accumulating preclinical and clinical evidence suggests antinociceptive effects of melatonin by acting on MT_1_ and MT_2_ membrane receptors (to reduce cyclic AMP) but possibly also (1) by indirectly activating opioid receptors, (2) by inhibiting the production of proinflammatory cytokines, (3) by activating γ-aminobutyric acid-A receptors, and (4) through its antioxidant effects [14]. Emerging evidence suggests that melatonin reduces pain in both preclinical and clinical (fibromyalgia) settings [15-17], in addition to multiple randomized controlled trials (RCTs) demonstrating efficacy for primary insomnia and delayed sleep phase syndrome [18]. After oral administration, melatonin undergoes first-pass hepatic metabolism [19], with subsequent secondary renal metabolism and elimination [20]. A review of studies involving varying doses [21] reported that oral administration of melatonin results in a transport maximum ranging 15-210 minutes, and a half-life ranging 28-126 minutes [21].

Thus, in the interest of further evaluating the analgesic efficacy of melatonin for NP, our objective is to conduct a double-blind RCT to compare the efficacy of melatonin to that of placebo in patients with chronic neuropathic conditions.

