### Design

This is a double-blind, randomized, controlled, 2-period, crossover trial comparing melatonin to placebo in adults with chronic neuropathic pain (Figure 1). Both treatment periods will be 5 weeks in duration, and the entire trial will be 10 weeks long for each participant. Participants will be randomized to one of the two treatment sequences. The randomization sequence will be generated using the web-based program randomization.com (Dallal, Tufts University). Participants in sequence 1 will take active melatonin capsules during the first 4 weeks of the trial (followed by a 1-week washout period) and will subsequently take inert placebo capsules for the next 4 weeks of the trial (followed by a 1-week washout period). Participants in sequence 2 will take inert placebo capsules during the first 4 weeks of the trial (followed by a 1-week washout period) and will subsequently take active melatonin capsules for the next 4 weeks of the trial (followed by a 1-week washout period). Figure 1 shows a schematic representation of the trial design.

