## Discussion

NP remains a challenging condition to treat, with current recommended pharmacological therapies providing only partial relief from pain, sometimes exacerbating other symptoms [41]. To the best of our knowledge, this proposed RCT is the first to investigate the safety and efficacy of melatonin for the treatment of NP. Given the potential improvement of pain and sleep with melatonin, we expect to observe a significant difference between the melatonin and placebo groups with respect to the primary outcome of pain and the secondary outcome of sleep in patients with NP. Although there has been some previous interest in the use of melatonin for pain management, few trials have been conducted in clinical chronic pain, and most of these have involved participants with fibromyalgia [15-17] and only one trial involved participants with NP [42]. Therefore, we expect that this trial will provide much needed evidence to further guide the appropriate use of melatonin in the management of NP.

Potential threats to this trial include challenges with patient recruitment, early dropouts, noncompliance, and protocol violations. However, the planned study design as well as our experience with similar previous chronic pain trials will mitigate these threats. In particular, careful and frequent follow-up of trial participants, timely management of treatment-emergent AEs, and open communication between participants and trial personnel are, once again, expected to minimize trial dropouts and thus maximize participant retention. Furthermore, as with our past RCTs, noncompliance, protocol violations, and early dropouts will be minimized by our proposed crossover design, thorough study participant teaching, and close weekly follow-up of participants. Variations in melatonin bioavailability across trial participants may increase the overall variability in trial results; however, compared to a parallel-group trial, our proposed crossover design will reduce the impact of such variability, whereby each participant acts as their own control.

In light of the current lack of desperately needed new improved NP therapeutics, this trial is expected to provide evidence for a safer and more effective treatment for NP. The development of this proof-of-concept RCT of melatonin in NP will facilitate future confirmatory RCTs and the implementation of melatonin into practice.

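### The primary mixed model is over-parameterised for a two-sequence, two-period crossover, so the treatment effect cannot be estimated as written and the result depends on which term is dropped

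*Protocol article*

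**What the plan says.** The Design section describes a "double-blind, randomized, controlled, 2-period, crossover trial comparing melatonin to placebo" and adds: "Participants will be randomized to one of the two treatment sequences". One sequence takes melatonin then placebo and the other takes the reverse, with a one-week washout after each four-week treatment.

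The Statistical Analysis section fits "A linear mixed model with sequence, period, treatment, and the first-order carryover effects as fixed effects and participant as a random effect". The model is to test for a treatment difference and "to estimate the least squares mean of the mean daily pain intensity for each treatment group, adjusting the carryover and period effects". The two treatments are then compared "on the basis of the least squares means and SDs from the linear mixed model". The main analysis uses participants who complete both periods, and secondary outcomes follow the same approach. Nothing in the article makes carryover conditional, exploratory or confined to a sensitivity analysis.

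The rest of the article relies on within-participant information. The Sample Size section starts from a within-participant variation of 2.5, and the Discussion defends the crossover as a design "whereby each participant acts as their own control".

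**The concern.** A two-by-two crossover gives four sequence-by-period means. Intercept, sequence, period, treatment and carryover make five parameters, so one of them must go before the model can be fitted. The article does not say which. That leaves the primary estimate, its standard error and its p-value to a software default or to a choice made later by the analyst, which pre-specification is meant to prevent.

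One of the possible choices also gives up the reason for using a crossover. Genuine adjustment for carryover in this design rests on period 1 alone, which conflicts with the own-control rationale and with the basis of the sample size.

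**Working it through.** **Inputs.** From the Sample Size section: difference 1.5, α 0.05 (taken as two-sided, because the alternative is stated as a difference), power 80%, variation 2.5, 21 participants raised to 24 completers. An even split, 12 per sequence, is assumed. From the Introduction: "a half-life ranging 28-126 minutes". The within-participant correlation ρ is not given, so a range of 0 to 0.8 is assumed.

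**1. The plan's own figure.** With 2.5 read as the SD of the paired difference (SDd):

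n = [2.5 × (1.960 + 0.842) / 1.5]² = 21.8

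This is close to the stated 21. Based on the t distribution, power is 74% at 21 and 80% at 24. If 2.5 is a within-participant variance, SDd = √(2 × 2.5) = 2.24, n is 18 (normal) or 20 (t), and power at 24 is 88%. If 2.5 is a within-participant SD, SDd = 3.54 and n is 44 to 46, which does not reproduce the plan. Both readings that come near 21 assume a paired comparison.

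**2. Estimability.** Code sequence, period and treatment as ±1. Carryover is 0 in period 1 and takes the code of the previous treatment in period 2.

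| Cell | Intercept | Sequence | Period | Treatment | Carryover |
|---|---|---|---|---|---|
| Melatonin first, period 1 | 1 | +1 | −1 | +1 | 0 |
| Melatonin first, period 2 | 1 | +1 | +1 | −1 | +1 |
| Placebo first, period 1 | 1 | −1 | −1 | −1 | 0 |
| Placebo first, period 2 | 1 | −1 | +1 | +1 | −1 |

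In every row, carryover = (sequence − treatment)/2. There are five columns and the rank is 4. Add any constant c to the treatment coefficient, 2c to carryover and −c to sequence: all four fitted means stay the same. The data therefore cannot identify the treatment coefficient. The random participant term describes covariance and adds nothing to the mean structure.

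**3. The two ways of making it run.** Treatment weights are on the cells in the order of the table.

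- Drop sequence, keep carryover: (1, 0, −1, 0). This is the period-1 melatonin mean minus the period-1 placebo mean. In 300 simulated trials with 12 per sequence, the mixed-model estimate equalled that difference to rounding error.
- Drop carryover, keep sequence: (½, −½, −½, ½). This is the usual within-participant crossover estimate.

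**4. Power under each, 24 completers.**

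- Crossover variance: SDd²/N = 6.25/24 = 0.260, so SE 0.51.
- Period-1 variance: 4σ²/N with σ² = SDd²/[2(1 − ρ)], which gives 2·SDd²/[N(1 − ρ)]. At ρ = 0.5 this is 12.5/12 = 1.04, so SE 1.02.
- Variance ratio: 2/(1 − ρ).

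Power is from the noncentral t with 22 degrees of freedom.

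| ρ (assumed) | Variance ratio | Period-1 power, SDd 2.5 (crossover 80%) | Period-1 power, within-participant variance 2.5 (crossover 88%) |
|---|---|---|---|
| 0 | 2.0 | 51% | 60% |
| 0.3 | 2.9 | 38% | 46% |
| 0.5 | 4.0 | 29% | 35% |
| 0.7 | 6.7 | 19% | 23% |
| 0.8 | 10.0 | 14% | 17% |

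Normal approximations are at most about four percentage points higher (55% at ρ = 0 and 15% at ρ = 0.8, with SDd 2.5).

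**5. Washout.** 7 × 24 × 60 / 126 = 80 of the longest half-lives cited.

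**The case against.** The strongest reply is that the trial may lose nothing in practice. Carryover is the last term listed, and software that discards the redundant column could leave sequence, period and treatment, with about 80% power. That is fair. A reader might infer from the text that the stated power is lost; the documents do not support so flat a claim. As written the model has no defined power, and the loss arises only if sequence is the term dropped. What remains is that the power-preserving route is not the carryover-adjusted analysis the article declares.

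The percentages are also open to challenge. The correlation is assumed, and the article does not say what kind of quantity 2.5 is. They are illustrative, but the direction is firm: for any non-negative correlation the variance at least doubles, and no value from 0 to 0.8 brings period-1 power to 80%.

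A separate analysis plan might settle the parameterisation. The article nevertheless states its model explicitly, so this is not a detail left for later. A plan that followed it would inherit the fault, and one that did not would contradict it. The washout diaries do not help, because the primary response is limited to the week-4 average.

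Two further inferences should be resisted. The mention of SDs could be read as planning a wrong error term, but it is more plausibly loose wording for model-based standard errors. And 80 half-lives could be read as excluding all carryover. It addresses drug elimination only; the Introduction itself describes circadian and mood effects and a two-way link between pain and sleep.

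**Conclusion.** The primary model is wrong as written. With four cell means and five mean parameters, the treatment effect is not estimable, and nothing else in the article repairs this. That conclusion is algebraic and needs no assumption beyond the stated design and model.

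The consequence for power is conditional. It falls to the period-1 column of the table if carryover is truly adjusted for, and is kept at 80% (or 88% on the variance reading) if carryover is dropped. Those figures rest on 24 completers split evenly, a true difference of 1.5, two-sided α of 0.05 and the assumed correlations. The fault extends to the secondary outcomes, which use the same approach. The SD wording is an editorial matter.

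**What to change.** Specify the primary model, and the model for the secondary outcomes, as fixed sequence, period and treatment with random participant and no carryover term. Report the within-participant treatment difference with its SE and 95% CI, and replace the reference to SDs with the SE of the difference.

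State that pharmacokinetic carryover is addressed by the existing washout, and acknowledge that any other persistence cannot be separated from sequence effects in this design. Report the period-1-only comparison as a labelled sensitivity analysis with its low precision noted. Do not let a carryover pretest choose the analysis.

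The cost is a few sentences of analysis text, settled before unblinding, with no new data or visits. The downside is that the primary result then assumes negligible carryover. With weights (½, −½, −½, ½), a difference in carryover between melatonin and placebo of size λ would shift the treatment estimate by −λ/2. The assumption should therefore be stated openly.
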